#### Statistical methods to handle missing data

2.6.2

All formal statistical analyses will follow the intention-to-treat principle. Estimates derived by fitting linear mixed models are valid in the presence of missing outcome values provided the missing data generating mechanism is missing at random (MAR). This particular MAR assumption allows all variables included in the analysis model to drive missingness. Multiple imputation will be employed should covariates be missing, or aspects of the interventions drive absence of outcomes. Details of any additional analyses will be described in the SAP.

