### Statistical analysis

2.6

The primary outcome, time to relapse from recovery, will be analysed using Cox regression, where time to relapse will be the dependent variable, with fixed explanatory variables of trial arm, and stratification factor (catchment area of the mental health service), and cluster-level balancing variables of general practice list size, and Index of Multiple Deprivation. The model will also contain a random intercept that varies at the level of the catchment area to account for general practice cluster effects.

This modelling will supply an estimate of the hazard ratio of relapse comparing Open Dialogue with TAU and an associated 95% confidence interval. In the (unlikely) event that covariates are missing or that aspects of the Open Dialogue intervention (e.g. number of contacts between participants and teams) drive censoring times, we will employ multiple imputation for survival outcomes as described in White and Royston [61].

Continuous secondary outcomes measured at several time points will be analysed using linear mixed models. In these models the available post-allocation measures of the secondary outcome variables form the dependent variable, with trial arm, time, trial arm x time interactions terms, stratification, and balancing variables as explanatory variables. To account for the correlation between repeated measures taken on the same subject, subject-varying random effects will be included in the model. To account for remaining correlation between outcomes from patients from the same cluster, a further cluster-varying random intercept will be included in the model.

Distributional assumption will be checked and continuous outcomes arising from skewed distributions suitably transformed before analysis.

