### Participant recruitment and retention

4.1

If a person presents to services and appears eligible, a local staff member asks if a researcher can make contact. Those who agree are contacted by a researcher with further information, and after time to consider (usually 48 h or as long as they need), they are asked for informed consent. If they lack capacity, consent via a personal (relative or friend) or nominated consultee (a local senior clinical professional consultee with no other involvement with the trial) may be sought [58], and reviewed at the point they regain capacity. Separate informed consent is sought from the family and carers of a purposive sub-sample of trial participants for questionnaires, and from all who attend a network meeting to audio-record that meeting.

Participants are also given a £15 shopping voucher for each interview and are reimbursed for any additional expenses (e.g. travel). For those participants who choose to withdraw from further participation, agreement is sought for access to their electronic medical records for the remainder of the study to allow for the primary clinical outcome to be collected.

Research staff are located within NHS sites, closely engage with clinical teams, and receive regular training, support, and supervision to effectively engage participants. Regular meetings with site-based Principal Investigators (PIs) and other senior clinical and management staff, and input from the Lived Experience Advisory Panel (LEAP) address any issues with participant recruitment and retention.

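### The stated imputation rule does not handle interview non-response driven by relapse or admission, although the trial extracts that state from records

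*Protocol article*

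**What the plan says.** Under Statistical analysis (2.6), the secondary models use every score obtained after allocation: "the available post-allocation measures of the secondary outcome variables form the dependent variable". The article then lists the fixed effects that go on the other side of the model: "with trial arm, time, trial arm x time interactions terms, stratification, and balancing variables as explanatory variables". To these fixed effects the plan adds random effects: "subject-varying random effects will be included in the model", together with a cluster random intercept. No relapse, admission or symptom variable is listed.

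Under Statistical methods to handle missing data (2.6.2), the mixed models are said to be valid if the mechanism is missing at random, and "This particular MAR assumption allows all variables included in the analysis model to drive missingness". The fallback follows: "Multiple imputation will be employed should covariates be missing, or aspects of the interventions drive absence of outcomes". The section closes with "Details of any additional analyses will be described in the SAP". In 2.6, the example given of an intervention aspect, for the survival analysis, is the number of contacts between participants and teams.

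Clinical state is collected separately from the interviews. A blinded panel dates recovery and relapse over two years from a summary built mainly from medical records (2.5, 4.2.2). Admissions and crisis referrals come from records (Tables 1 and 2). For people who withdraw, "agreement is sought for access to their electronic medical records for the remainder of the study" (4.1).

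**The concern.** After a mental health crisis, relapse or a hospital stay at the time of a visit is a natural reason to miss an interview, and also a reason for a poor score. The mixed model handles such absence only so far as it can be predicted from the model terms and the person's other observed scores of the same outcome. A relapse since the last completed visit is only partly visible there. QPR and CSQ-8 are not collected at the first research interview (Table 2), so someone who misses the 3-month visit has no earlier score at all on these two measures. BPRS is collected at that interview but is not in the model.

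The stated trigger does not fill this gap, because clinical state is neither a missing covariate nor, on its face, an aspect of the intervention. At stake are the arm comparisons of service-user defined recovery, quality of life and satisfaction. Different retention by arm is plausible: continuity of practitioners and open discharge are what Open Dialogue changes (section 3), and interviewers know the allocation and work closely with the clinical teams (2.5.2, 4.1).

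**Working it through.** **1. The plan's own figures.** The article gives no figure for interview non-response. The relapse risks used below rest on its sample-size section (2.5.1), so that was checked first.
- Freedman, two-sided 5%, 90% power: ((1 + 0.589)/(1 − 0.589))² × (1.960 + 1.282)² = 157.06. Stated: 157.
- 157 × 1.68 = 263.8. Stated: 264.
- 264/0.49 = 538.8. Stated: 538.

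All agree to rounding.

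**2. Relapse risk by arm.** Let p be the TAU risk at 24 months. With HR 0.589 and a 49% average, (p + 1 − (1 − p)^0.589)/2 = 0.49. This gives p = 0.58 for TAU and 0.40 for Open Dialogue.

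**3. Assumptions that are not in the article.** Relapse lowers the score by d = 0.8 SD. Non-response is 20% without relapse and 30% or 50% with relapse.

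**4. Limiting case: earlier scores carry no information on the relapse.** Among people interviewed, the relapsed share is s = r(1 − m₁)/[r(1 − m₁) + (1 − r)(1 − 0.2)], where r is the relapse risk and m₁ the non-response after relapse. The estimated arm difference is d × (s in TAU − s in Open Dialogue). The true difference is 0.8 × (0.58 − 0.40) = 0.144.

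| Non-response after relapse, TAU / Open Dialogue | s, TAU | s, Open Dialogue | Estimate (SD) | Bias (SD) |
|---|---|---|---|---|
| 50% / 50% | 0.290/0.626 = 0.463 | 0.200/0.680 = 0.294 | 0.135 | −0.009 |
| 50% / 30% | 0.290/0.626 = 0.463 | 0.280/0.760 = 0.368 | 0.076 | −0.068 |
| 30% / 50% | 0.406/0.742 = 0.547 | 0.200/0.680 = 0.294 | 0.202 | +0.058 |

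**5. Four visits, earlier scores used.** Simulation with visits at 3, 6, 12 and 24 months, 200,000 per arm, the same non-response rates, within-person correlation 0.3 to 0.5, and a repeated-measures likelihood model fitted by arm. In this set-up relapse persists once it has occurred, so earlier scores carry part of the information. At d = 0.8 the bias in the 24-month difference was:
- 50% in both arms: about −0.01 SD.
- 50% TAU, 30% Open Dialogue: −0.05 to −0.06 SD.
- 30% TAU, 50% Open Dialogue: about +0.05 SD.

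At d = 0.5 the two unequal cases gave about 0.03 to 0.04 SD. A more extreme contrast, 60% TAU against 30% Open Dialogue, gave 0.06 to 0.10 SD. Adding relapse state as an auxiliary variable brought every estimate to within about 0.005 SD of the true difference, which is close to simulation error.

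**6. Scale.** With 270 per arm and the plan's design effect, the standard error of a difference in SD units is √(1.68 × 2/270) = 0.11 before any missing data. A bias of 0.05 to 0.07 SD is roughly half of that.

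**The case against.** The strongest reply is that auxiliary variables and departures from missing at random are normal SAP content, and that 2.6.2 refers to the SAP. This stands in part. A reader might infer that relapse-driven missingness will never be corrected, and the article does not support that: the SAP is not shown and could widen the rule. But the article does state a rule for when imputation is used, and an SAP that follows it would not reach clinical state.

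A reader might also infer that missingness is assumed to depend only on arm, time and cluster variables. That is wrong. A likelihood model with repeated scores and subject random effects also conditions on each person's other observed scores, which removes part of the bias.

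Thirdly, if Open Dialogue keeps relapsed people in contact better, that could itself count as an intervention aspect and trigger imputation. This is arguable. Even then, the rule does not say that clinical state would enter the imputation model, and imputing without it would leave the bias.

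Other limits also stand. Nothing in the article shows that relapse drives missed interviews. The illustration counts anyone relapsed by 24 months; relapse current at the visit would be less common, so the bias would probably be smaller. The 5% attrition in 5.1 is not described as record-based and says nothing about interviews. Records access after withdrawal is sought, not assured. Part of the relapse summary comes from research contacts, so it is less informed for people who miss interviews. The article also does not claim unconditional validity for the mixed models.

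**Conclusion.** The point holds as a gap in the stated rule, not as a demonstrated bias. Under 2.6.2 as written, interview non-response driven by relapse or admission between visits is not handled, although the trial extracts that state for most participants, including those who withdraw but agree to records access. If the mechanism is the same in both arms, the bias in the arm difference is about 0.01 SD and can be ignored. If retention of relapsed participants differs by arm, it could be about 0.05 to 0.07 SD in either direction, against an assumed true difference of 0.144 SD. These sizes rest on assumed non-response rates and an assumed 0.8 SD relapse effect; a smaller effect or a smaller contrast in retention gives less.

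It concerns the secondary interview outcomes only. A reader might extend it to time to relapse, but that outcome is rated mainly from records and does not depend on these models. The change is worth making because it is cheap and the direction of any bias cannot be known in advance.

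**What to change.** Widen the rule in 2.6.2, and carry it into the SAP, so that imputation of missing QPR, EQ-5D-5L and CSQ-8 scores is pre-specified and does not wait for the present triggers. Impute separately by arm and respect the clusters. Use as auxiliaries the panel-rated relapse or recovery state in the interview month, inpatient status at the interview date, and admissions and crisis referrals to date. These enter the imputation model only, so the intention-to-treat comparison is unchanged. Fit the planned mixed model to the imputed data and report it alongside the un-imputed mixed model. Which of the two is labelled the main analysis is a matter of preference, provided it is fixed beforehand. Report interview non-response by arm and relapse state.

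The cost is wording and a few days of analysis, without new data collection. The secondary analysis must wait for the panel ratings, multilevel imputation is somewhat more complex, and the auxiliaries are weaker for people with few research contacts or no agreement to records access.

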## Intervention delivery

3

Open Dialogue teams offer care from initial presentation in crisis through to discharge from the service, typically through ‘network meetings’ which include the service user, people they identify as important to them such as family members, and two or more Open Dialogue Practitioners. The agenda is set by the network, and there is a strong emphasis on service-user participation in any treatment decisions. Wherever possible, the same practitioners remain with the network throughout. Teams are multidisciplinary, typically including nurses, social workers, peer practitioners, clinical psychologists, occupational therapists, and psychiatrists, all of whom have undertaken an Open Dialogue training programme. Services are underpinned by the seven key principles of Open Dialogue: (1) Immediate Help; (2) A Social Network Perspective; (3) Flexibility and Mobility; (4) Responsibility; (5) Psychological Continuity; (6) Tolerance of Uncertainty; and (7) Dialogue and Polyphony [56]. They are ‘needs-adapted’ and network meetings take place as little or often as required by the network, perhaps occurring twice weekly in the time immediately after referral, moving to weekly or fortnightly as treatment progresses, whilst also working flexibly in collaboration with other services [48]. There is an ‘open discharge policy’, with service users able to ask for further network meetings at any point after discharge from the service, ideally with the same practitioners.

TAU is current routine crisis care and continuing community care, as delivered by English mental health services. This is based on a model which comprises a number of multi-disciplinary teams, the provision of care coordination, and a range of community and in-patient interventions and support.

 Participants in both trial arms may be offered any intervention they would ordinarily have access to individual psychological and pharmacological interventions, social, and housing support. The duration of contact is determined by each team, based on clinical need. Those with complex problems may receive continuing care for the duration of the study. Open Dialogue is not offered to those in the TAU arm. The provision of mental health services after the follow-up period has ended will be the responsibility of the participants' current mental healthcare provider.

All teams in the trial were required to deliver care adequately (according to adherence and fidelity criteria detailed below), and to produce a site-specific operational policy which described care pathways and met trial requirements for Open Dialogue services prior to recruitment of trial participants. All Open Dialogue trained staff are offered annual refresher training.

### Monitoring intervention delivery

3.1

The fidelity of service delivery in both the Open Dialogue and TAU teams is assessed to ensure that that the core structural components of services are delivered as intended. The ODDESSI fidelity measure [3] draws on an existing measure [44], and is based on interviews with service staff and review of documentation. Four key aspects of service functioning are rated: (1) Team structure and culture, (2) Access and engagement, (3) Delivery of care, (4) External support. To meet fidelity services must score at least 2.4 of 4 on each of the above.

The extent the core therapeutic components of Open Dialogue are delivered within a network meeting is measured using the Open Dialogue Adherence scale [32] which was developed from (and closely aligned with) a previous adherence measure [44]. Audio recordings are assessed by trained raters and scored according to the key elements of dialogic practice [32,43] and then rated as ‘acceptable’ or ‘unacceptable’. In ‘acceptable’ tapes at least two thirds of statements used by practitioners are dialogic (rather than monologic) and less than two statements are patronizing or disrespectful, and at least 10 out of 12 of the items based on the key elements of dialogic practice score ‘acceptable’.

All Open Dialogue and TAU teams are monitored prior to participant recruitment and at 6-monthly intervals throughout intervention delivery. Where fidelity or adherence is identified as falling below the pre-determined levels, remedial action is taken, and recruitment may be stopped locally in that cluster if the problem persists despite remedial action. Actual intervention or ‘dose’ received: the number, date, and mode of delivery of clinical meetings, is also recorded at a participant level.

## Research processes

4

### Participant recruitment and retention

4.1

If a person presents to services and appears eligible, a local staff member asks if a researcher can make contact. Those who agree are contacted by a researcher with further information, and after time to consider (usually 48 h or as long as they need), they are asked for informed consent. If they lack capacity, consent via a personal (relative or friend) or nominated consultee (a local senior clinical professional consultee with no other involvement with the trial) may be sought [58], and reviewed at the point they regain capacity. Separate informed consent is sought from the family and carers of a purposive sub-sample of trial participants for questionnaires, and from all who attend a network meeting to audio-record that meeting.

Participants are also given a £15 shopping voucher for each interview and are reimbursed for any additional expenses (e.g. travel). For those participants who choose to withdraw from further participation, agreement is sought for access to their electronic medical records for the remainder of the study to allow for the primary clinical outcome to be collected.

Research staff are located within NHS sites, closely engage with clinical teams, and receive regular training, support, and supervision to effectively engage participants. Regular meetings with site-based Principal Investigators (PIs) and other senior clinical and management staff, and input from the Lived Experience Advisory Panel (LEAP) address any issues with participant recruitment and retention.

### Data collection

4.2

Primary data are collected during research interviews and are extracted from electronic medical records (see Table 2 for a full schedule of data collection).

**Table 2 t0010:** Data collection time-points.

Data source	Data collected	True baseline (crisis)	First research interview	3 months	6 months	12 months	24 months
RCT participants	Sociodemographic information		X				
	Brief Psychiatric Rating Scale (BPRS)		X				
	Health related quality of life (EQ-5D-5L)		X	X	X	X	X
	Client Services Receipt Inventory (CSRI)			X		X	X
	Social Provisions Scale (SPS)		X	X	X	X	X
	Lubben Social Network Scale (LSNS-6)		X	X	X	X	X
	Questionnaire about the Process of Recovery (QPR)			X	X	X	X
	Client Satisfaction Questionnaire (CSQ)			X		X	X
	Modified Dyadic OPTION scale			X	X		X
Review of records	• Diagnoses (if any) • Drug/alcohol misuse • Contact with secondary mental health services and crisis referrals • Number of hospital visits • Inpatient stays • Other long-term health problems	X (Extracted for the 6 months prior to baseline)					
	Number of clinical meetings	Ongoing throughout trial participation					
	Relapse and recovery summary	Primary outcome assessed at 24 months					
	Hospitalisation	For the 6 months prior to baseline, and at 12 and 24 months					
	Crisis referral	For the 6 months prior to baseline, and at 12 and 24 months					

#### Baseline and follow-up research interviews

4.2.1

The baseline timepoint is the date of the crisis referral. This referral takes place after cluster randomisation, but before a potential participant has been assessed as meeting eligibility criteria prior to consent. The first research interview is conducted as close as possible to the date of the crisis referral (baseline) after consent is provided. Research interviews either occur in person (i.e. at the research site or at participant's homes) or over the telephone (the primary method of data collection during the COVID-19 pandemic). Follow-up interviews are undertaken at 3, 6, 12, and 24 months from baseline (see Fig. 1).

**Fig. 1 f0005:**
[figure not shown]
Study design.

#### Electronic medical records

4.2.2

After consent, baseline data are extracted from medical records for the date of the crisis referral and for the 6-months prior, and further service use data collected throughout the follow-up period. The monthly summary to be assessed for the primary outcome is created primarily from electronic medical records after completion of trial participation.

#### Family and carer interviews

4.2.3

Research interviews asking about shared decision-making, carer burden, and satisfaction also take place with a family member or carer of a sub-sample of participants (20%) at 3, 6, and 24 months from the date of the main trial participant's baseline.

### Data management

4.3

Trial participants' and carer's interview responses are collected on paper Case Report Forms (CRFs) and stored securely in locked filing cabinets, or electronic CRFs saved on secure shared drives on password protected computers within each trial site. Participants are identified only by a study ID on all CRFs (so they are pseudonymised). Files which include participants' names or contact details (consent forms and a trial management log) are stored in a separate physical or digital space. Data are only transferred where needed and each researcher is responsible for following their institution's protocols for safe data transfer. Only the CI and the named research team have access to personal data.

Data for fidelity and adherence ratings are stored electronically in a password protected file on a password protected computer, separate from any personally identifiable information. Recordings are uploaded to the Data Safe Haven at University College London (UCL).

Pseudonymised trial participant data are entered into a database via a web-based data entry system (InferMed MACRO) with access restricted to specific researchers or regulatory authorities, and for a specified purpose. The system is compliant with Good Clinical Practice [24] and has a full audit trail. The research team ensure data quality through regular reviews of the data and will carry out final data quality checks and cleaning before the database is locked prior to data analysis. The full details of the planned statistical analyses will be outlined in the SAP, which will be signed off before database lock.

Participant data will be stored securely for 10 years following completion of data collection. The trial is registered in accordance with the General Data Protection Regulation [16].

## Trial management, oversight, and monitoring

5

The trial is managed by the Chief Investigator (SP), Principal Investigators in each study site, and a Trial Management Group consisting of co-investigators, trial statisticians and the trial manager. Oversight is provided by a Lived Experience Advisory Panel (LEAP), an independent Programme Steering Committee (PSC), and an independent Data Monitoring Committee (DMC). All changes to trial protocol are reviewed and agreed by the PSC, and DMC if relevant, prior to implementation. Any protocol amendments are submitted to the Ethics Committee for review and if approved, circulated to trial sites and research staff.

The trial sponsor (North East London NHS Foundation Trust) also provides oversight, cover for any harm which may arise from trial participation, and audits the trial.

The reporting of serious adverse events is carried out in accordance to the UK policy framework for health and social care research [24]. Serious adverse events (defined in this trial as an untoward medical occurrence which is life threatening, requires hospitalisation, causes a persistent or significant disability, congenital abnormality, or birth defect or which results in death) will be described from a participant's baseline crisis, following their consent to participate in the study: either on review of patient notes, or as disclosed to researchers.

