### Participants' eligibility criteria

2.4

Participants who present to one of the participating mental health services who meet criteria for the crisis and continuing care pathway, and who are registered with a GP within a trial cluster are provided with Open Dialogue or TAU depending on their cluster. They may present by any route permitted within the service's local policies and procedures (for example, referral by a GP, an Emergency Department or other specialist service, or admission into an inpatient ward). There are further eligibility criteria for research participation:•Evidence of a mental health crisis indicated by (a) a rating of A-C on the UK Mental Health Triage Scale [53], which indicates either an emergency, very urgent or urgent response is needed based on a high risk of harm self or others and/or rapidly increasing symptoms of psychosis or severe mood disorder**,** (b) an admission to an inpatient ward or (c) being accepted into the care of a mental health crisis service•18 years of age or more•Sufficient English language abilities to participate in the research

Exclusion criteria are as follows: a diagnosis of dementia or an acquired cognitive impairment, a primary diagnosis of a learning disability or substance misuse, having no fixed abode, being under the care of forensic mental health services, and having previously received Open Dialogue.

Recruitment to the study was also not possible for those who are already participating in another research project that may impact their care in this trial, or if recruitment to the study would pose a risk of harm to the participant, study clinicians, or researchers.

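### The SAE definition omits prolongation of an existing hospital stay although participants can enter as inpatients, and the stated start of the SAE window leaves the status of the qualifying admission unclear

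*Protocol article*

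**What the plan says.** All places are in the protocol article.

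- **Seriousness criteria (section 5, Trial management, oversight, and monitoring).** An SAE is "defined in this trial as an untoward medical occurrence which is life threatening, requires hospitalisation, causes a persistent or significant disability". The list goes on to congenital abnormality, birth defect and death, and ends there.
- **SAE window (same section).** SAEs are to be described from the participant's "baseline crisis, following their consent to participate in the study: either on review of patient notes, or as disclosed to researchers".
- **Baseline (section 4.2.1).** "The baseline timepoint is the date of the crisis referral". On the order of events: "This referral takes place after cluster randomisation, but before a potential participant has been assessed as meeting eligibility criteria prior to consent".
- **Entry by admission (section 2.4).** Two of the three alternative ways to show a crisis are "b) an admission to an inpatient ward or (c) being accepted into the care of a mental health crisis service". Permitted routes of presentation include "referral by a GP, an Emergency Department or other specialist service, or admission into an inpatient ward".

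**The concern.** The trial recruits some people who are already on a ward, or who are admitted because of the crisis that makes them eligible. For them a seriousness test based on needing hospital care works poorly in two ways.

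First, a person who is already in hospital cannot newly require hospitalisation. If a harmful event during the index stay only lengthens that stay, no listed criterion applies and the event goes unreported as an SAE. These participants were judged ill enough to be admitted, so it is a poor place for a gap in safety capture.

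Second, if the window opens at the crisis referral, the qualifying admission lies inside it and can meet the hospitalisation criterion. An SAE listing would then hold events that brought people into the trial beside events that happened to them afterwards, and a reader could not tell them apart.

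**Working it through.** No figure in the plan is at issue and no formula applies. The check sets the provisions side by side.

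**Step 1: prolongation.** The section 5 definition is introduced as the one used in this trial, and its list is closed: life threatening, requires hospitalisation, persistent or significant disability, congenital abnormality or birth defect, death. Take a participant who qualified through route (b) in section 2.4 and is on the ward when a harmful event occurs.

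| Consequence of the event | Listed criterion met? |
|---|---|
| Life threatening | Yes |
| Lasting or significant disability | Yes |
| Death | Yes |
| Longer index stay only | No |

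Only the last row is missed. Table 1 in section 2.5 records the number and length in days of psychiatric admissions over 24 months, so the extra days would appear there, but as service use and not as harm. This step does not depend on how the window is read.

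**Step 2: start of the window.** The order of events under section 4.2.1 is cluster randomisation, crisis referral (baseline), eligibility assessment, consent, first research interview. The section 5 wording can be read in two ways:

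- *Reading A:* once a person has consented, SAEs are collected back to the crisis referral. The qualifying admission is then inside the window.
- *Reading B:* only events after consent count. A qualifying admission that began before consent is then outside it.

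Reading A is the more natural. Under B the reference to the baseline crisis would do no work. Section 4.2.2 also has records read back to the referral date after consent, and section 5 names review of patient notes as a source of SAEs. This supports A without proving it.

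**Step 3: status of the qualifying admission under A.** The event must be an untoward medical occurrence that requires hospitalisation. A crisis leading to admission can be classed that way. The article does not say whether it should be, so six services could classify the same kind of admission differently. Section 2.5.2 adds that the researchers who collect outcome data and work with clinical teams are not blind to allocation.

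**Step 4: size.** The share of participants entering by admission is not given. Entry routes (a) and (c) need no admission, so only part of the sample is affected. For scale only: each 10 percentage points of the 570 planned participants would be 0.10 × 570 = 57 qualifying admissions whose status is unclear. This is not an estimate of the number.

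**The case against.** The strongest reply is that this is a condensed article. It gives safety reporting a few lines and refers to the UK policy framework, and a rule for the index admission commonly sits in the full protocol. Under reading B the question of the qualifying admission also falls away. This largely stands for the qualifying admission: the lack of an exemption here is weak evidence that none exists, and what remains is a start point that should be worded clearly. It does not dispose of the missing prolongation criterion, because the article sets out the definition as the trial's own and lists it down to birth defects.

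A second reply is that starting at baseline is sensible. Under sections 2.4 and 3, allocated care follows the cluster from presentation, so exposure begins before consent and an early admission may be a consequence of that care. This also stands. It argues against removing the index admission from the SAEs and against starting risk time at consent, since either could discard early harm on a judgement that unblinded staff may be making.

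A reader might infer more than the text supports:

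- *That every hospitalisation is an SAE.* The definition needs an untoward medical occurrence that requires hospitalisation.
- *That harm on the ward is missed altogether.* Life-threatening, disabling and fatal events are captured.
- *That a between-arm SAE risk ratio is diluted by a calculable amount.* The article says only that SAEs will be described. It plans no such ratio, and neither the entry share nor the SAE risks are given.
- *That the death rate is materially understated because nobody who dies before consent joins the trial.* The logic is right, but no death-rate comparison is planned in the article and the length of the gap is not stated. Section 4.1 gives only the usual time to consider, 48 hours or as long as needed.

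**Conclusion.** The point holds in two parts of unequal strength. The omission of prolongation is firm: as written, a harmful event whose only consequence is a longer index stay is not an SAE, in a trial that admits inpatients. The second part is conditional. On the more natural reading of the window, the qualifying admission can count as an SAE and be mixed with later harm. On the other reading, the defect is an unclear start point.

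Neither part touches the primary outcome, and neither can be sized from the documents. The conclusion assumes that the definition in the article is the one sites apply, and that the full protocol, which is not shown, does not already settle the window and the index admission.

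**What to change.** 1. In section 5, add prolongation of an existing inpatient stay to the SAE criteria.
2. Reconcile sections 2.4, 4.2.1 and 5 so that the start of the SAE window is stated once, relative to both crisis referral and consent.
3. Keep the baseline start. Flag the admission that met the entry criterion, and tabulate it and other events between crisis and consent by arm, separately from later SAEs. Nothing is removed from the record, and a reader can see entry events and new harm apart.

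The cost is an amended definition, some re-coding of SAE listings and a few more reportable events. Hospitalisation and inpatient stays are already taken from the records (Table 2, section 4.2), which should supply most of what the flag needs. Whether an event lengthened a stay will need a judgement from the notes.
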